### **3.2 PRIMARY OUTCOME**

- Number of participant touch points defined as a participant-clinician interaction (outpatient appointment or equivalent) between the treating team and the participant from the participant diagnosis (defined as the date of attendance at diagnostic clinic) to the offer and prescription\* of the first adjuvant cancer treatment (see Appendix A for definitions). In the event of the participant declining further treatment the date of offer should be used.

For those participants receiving bridging therapy, the date of the confirmation of adjuvant systemic therapy (endocrine or chemotherapy) will be used.

\*Defined as the date prescription is documented as being issued in the clinic appointment or letter sent to GP to request prescription or treatment entered into Chemocare or equivalent.

### **3.3. SECONDARY OUTCOMES**

- Time in days between the participant diagnosis (defined as the date of attendance at diagnostic clinic) and the offer and prescription of the first adjuvant cancer treatment (chemotherapy, radiotherapy or endocrine therapy)
- Time in days between the participant diagnosis (defined as the date of attendance at diagnostic clinic) and the start of the first adjuvant cancer treatment (chemotherapy, radiotherapy or endocrine therapy)

- Alteration in recommended treatment sequence. This would be defined as a when a participant in the intervention arm, as a result of the RS results from the core biopsy, receives neo-adjuvant treatment rather than proceeding directly to surgery. The clinical touchpoints, HADS and HRUQ would no longer be collected but the participants would be followed up until completion of treatment for final post-operative pathology.
- Participant reported anxiety score HADS score at the post-operative result clinic and following the offer of adjuvant treatment
- Health system cost impact analysis comparison of the intervention arm with the control arm
- Correlation of preoperative staging with postoperative pathological staging
- Rate of failure of the Oncotype DX® assay (RS result cannot be issued) on diagnostic core biopsy specimen

### 3.4 STUDY FLOW CHART

[figure not shown]

## **4.0 RECRUITMENT PROCESS**

### **4.1 ELIGIBILITY**

#### **4.1.1. INCLUSION CRITERIA**

- Male or female  $\geq 18$  years of age
- Oestrogen receptor positive HER2 negative invasive early stage breast cancer confirmed on diagnostic core biopsy, as per definition of hormone receptor status in NICE DG34 guidance
- Pre-operative staging of grade 2 cancer  $\geq 20$  mm on all imaging modalities or grade 3 cancer of any size and N0 on axillary staging or any size or grade which is N1 on preoperative axillary ultrasound scan +/- FNA or core biopsy\*
- Surgery planned as first definitive treatment
- Fit for adjuvant chemotherapy
- Able to provide written or remote (eConsent or postal) informed consent
- Able to complete questionnaires and study assessments

\* If local reimbursement available for N1 patients oncotype

#### **4.1.2 EXCLUSION CRITERIA**

- ER negative or HER2 positive breast cancer
- N2 disease on pre-operative staging
- Planned for neo-adjuvant systemic therapy (endocrine bridging therapy for a delay in planned surgery is permitted)
- Unfit for surgical treatment or systemic chemotherapy
- Are unable to provide informed consent
- Have co-existing malignant disease only if this would affect the study in the investigator's opinion
- Are unable to complete study questionnaires even with the assistance of the study nurse
- Are already participating in another clinical trial

## **4.2 IDENTIFICATION AND APPROACH**

Patients will be referred to the breast unit following a GP referral or a suspicious mammogram screening result, and standard diagnostic screening tests completed as routine care. Patient cases will be discussed in the diagnostic MDT meeting, consisting of oncologists, surgeons, radiologists, pathologists and breast care nurses where the pre-test patient management plan will be determined. Breast cancer and disease staging will be confirmed and potential participants suitable for the study will be identified.

Potential participants will be seen in a pre-operative diagnostic clinic visit where their treating clinician will inform them of their cancer diagnosis. The treating clinician will discuss the study with the patient. If interested, they will be given a study Participant

Information Sheet (PIS) and a copy of the consent form to take away to consider. If all the required test results have been received and eligibility confirmed the potential participant, with their permission, will then be referred to the site research team.

If any results required to confirm eligibility are outstanding (e.g. HER2) at the diagnostic clinic appointment, the process as above can still be followed provided it is clear that their eligibility is dependent on any outstanding test results. The potential participant will only be approached by the site research team once eligibility is confirmed. Alternatively, the information (e.g. PIS) can be posted to the patient following the appointment along with the accompanying invitation letter ahead of eligibility being confirmed.

[figure not shown]

Figure 1. Pathways to **patient approach**

### 4.3 INFORMED CONSENT

Provided permission from the patient has been received, once eligibility has been confirmed the site research team will telephone or see the potential participant at the next appointment. This will occur no earlier than 24 hours after the PIS was provided to allow time for it to be read. The site research team will answer any questions the patient might have and if they are still interested in participating, will proceed to take informed consent. Consenting will be primarily be by remote consent, however, if the potential participant is scheduled to attend a planned follow-up clinic, the informed consent process may be conducted face to face. Informed consent will be taken by a study clinician or research nurse if authorised to do so on the delegation log and documented in the participants medical records.

For remote consent, either e-consent using DocuSign® or postal consent, if they are unwilling or are unable to access the internet, will be taken following real time discussion. In the event of postal consent being used, provided the participant has

confirmed that they have signed during the call, this will be taken as the date of consent. Due to the potentially tight study timelines, baseline assessment will be allowed to be completed before the consent form is received back and countersigned by the delegated site researcher. The participant returning the form at the next clinical appointment will be acceptable. For informed consent taken during face to face clinics either paper or e-consent methods will be used.

A copy of the consent form will be uploaded into the study REDCap Cloud data capture system (RCC) for monitoring purposes. The identity of the participant (if unknown to the site research team at the time of consent) will be checked at the next face to face clinic appointment to verify that the person that consented is who they say they are.

The study team will inform the participant's GP and clinical care team of their participation.

Study documents will not be translated into other languages. However, the use of hospital translation services will be permitted to support inclusion from all demographic groups.

Reasons for not taking part in the study will be closely monitored by Hull Health Trials Unit (HHTU). Participants do not have to provide a reason for their decision.

The PI has overall responsibility for informed consent of participants at site and must ensure that anyone delegated responsibility to conduct informed consent is duly authorised, trained and competent to undertake consent according to the protocol and Good Clinical Practice (GCP).

Once consented, the participant will then complete the baseline assessment which includes the Hospital Anxiety and Depression Scale (HADS) before being randomised.

#### **4.3.1 PARTICIPANTS UNABLE TO GIVE CONSENT**

For participants unable to read/sign the consent form, and for those with problems of comprehension (in accordance with the Mental Capacity Act 2005), study participation and informed consent will not be sought.

#### **4.3.2 WITHDRAWAL OF PARTICIPANTS**

Participants remain free to withdraw at any time from the study without giving reasons and without prejudicing their further treatment. During discussions around the participants withdrawal, they should be provided the option of withdrawing fully or just from the study questionnaires (e.g. no further contact with study team but touch points still recorded).

If the participant is willing to provide a reason for the withdrawal, this should be recorded when completing the withdrawal on the study database, although the participants' right not to give a reason must be respected throughout. Data collected up

to the point of participant withdrawal will be included in data analysis but no further contact will be made with the participant.

The informed consent form includes a statement on the use of data after a participant withdraws from the study.

#### **4.4 ENROLMENT AND RANDOMISATION**

A purpose built, secure web-based data capture system with integrated randomisation will be provided and maintained by HHTU. A HHTU statistician, independent from the study team, will prepare a randomisation schedule. Patients will be randomised to Intervention and Standard Arm in 2:1 ratio using random permuted blocks, stratified by site and disease staging to balance potential confounding factors. The standard clinical care pathway at participating sites will introduce some variation in terms of number of patient clinical touch points. Disease staging may alter the complexity and choice of treatment patients receive, and therefore the number of clinical touch points. It is therefore important to stratify randomisation by both site and disease staging. As this is not a blinded study, research teams and participants will know the study arm to which they have been allocated.

When a participant is enrolled on RCC, a Subject ID Number will be automatically generated that will be entered on all study documents from that point onwards. Prior to randomisation, the study team will be asked to confirm informed consent has been taken. Participants will then be randomised to Standard or Intervention arms with the site receiving immediate notification of allocation. HHTU will receive an automatic email notification to flag that a randomisation event has occurred.

Authorised trial staff with delegated responsibility for randomising patients will access the secure online randomisation system administered by HHTU. User accounts will be set up for delegated site staff by HHTU once all the necessary trial documentation and approvals for participation in the study have been received. Randomisation will not be activated at individual sites until the site green light has been confirmed.

#### **5.0 DATA COLLECTION**

##### **5.1 STUDY VISIT SCHEDULE**

The study visit schedule will follow routine clinical care pathways – the only additional non-routine visit will be a telephone or video call to obtain informed consent and conduct baseline questionnaires. There will be no change to participant standard pre-operative investigations or clinic attendances, and these will be conducted either remotely or Face to Face, depending on current practice at site and following current guidance for COVID-secure appointments

Visits will be scheduled by the treating clinicians according to site clinical care pathway protocols and as such there is no visit window for any of the visits. Informed consent must be taken before surgery so that participants can be randomised into the standard or intervention arm.

Data on the time taken and the number of clinical touchpoints/visits from the initial patient approach to the offer of adjuvant cancer treatment by both groups will be collected as a study outcome. At baseline, participants will complete the Hospital and Anxiety Scale (HADS) as part of the baseline assessment. The HADS and a health resource utilisation questionnaire will then be completed following the post-operative clinic and following the offer of adjuvant treatment. In the event of the two follow-up events being the same date only the following the post-operative clinic questionnaires will be completed.

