### 3.1 INTERVENTIONS

For participants in the Standard arm, standard practice will be followed at each site for ordering and acting on the Recurrence Score® (RS®) result. The Oncotype DX® test is performed on excision samples obtained during surgery#.

#Participants receiving endocrine bridging therapy are eligible for the study provided the reason is that there has been a delay in planned surgery. Patients prescribed neo-adjuvant endocrine or chemotherapy for the purpose of downstaging are **not** permitted. In the event of the participant having received endocrine bridging therapy prior to surgery, as per routine practice, the use of the core biopsy for testing is permitted in the standard arm provided it is still ordered in the post-operative setting.

For participants in the Intervention arm, the Oncotype DX® test will be performed on the core biopsy that was taken at the time of diagnosis and the results of the Oncotype DX® test will be available to be discussed at the post-operative MDT meeting. The discussion will support decision-making on treatment options.

A failure of RS scores on the diagnostic biopsy sample would mean the test result being unavailable to support adjuvant treatment decisions for participants in the Intervention Arm. In the event of a failure on the diagnostic biopsy sample, the excision sample will be retested as per the surgical excision biopsy group. They will continue in the study in their original allocated group, being included in the primary intention to treat analysis.

Planned surgery will not be delayed if RS® results are unavailable and any change to the treatment recommendation will be recorded and discussed with the participant at an additional routine clinic appointment if required. If there is no change to the treatment recommendation, it will be left to the Centre's discretion whether to discuss the results with the patient before surgery but intentions of the centre will be recorded. If the event the decision is made to change the treatment pathway with the patient subsequently receiving neo-adjuvant or endocrine therapy prior to surgery, the clinical touchpoints, HADS and HRUQ would no longer be collected but the participants would be followed up until completion of treatment for final post-operative pathology.

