## Table of data collection

|                                                  |                                                                                                                                                                                                                                                                                                                                      |
|--------------------------------------------------|--------------------------------------------------------------------------------------------------------------------------------------------------------------------------------------------------------------------------------------------------------------------------------------------------------------------------------------|
| Baseline data                             | 
 
○ Consent
 
○ Demographics (year of birth, age, sex, ethnicity)
 
○ Histology / radiology / pathology reports on diagnostic investigations
 
○ Disease staging – TNM grading
 
○ HADS
 
○ Randomisation
 
                                         |
| Post consent                              | 
 
○ Oncotype DX® test date ordered on diagnostic biopsy (Intervention Arm only)
 
                                                                                                                                                                                                      |
| Surgery                                   | 
 
○ Results of surgery – histology, radiology, pathology reports
 
                                                                                                                                                                                                                     |
| Post-op results clinic                    | 
 
○ Oncotype DX® test date ordered (Standard Arm only) RS results delivered (intervention)
 
                                                                                                                                                                                           |

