| One week after Post-op Clinic (± 4 days)  | 
 
○ HADS and HRUQ
 
                                                                                                                                                                                                                                                                    |
| ~2 weeks after Post-op clinic             | 
 
○ RS results delivered (Standard arm only)
 
                                                                                                                                                                                                                                         |
| Adjuvant treatment offer and prescription | 
 
○ Treatment type (specifics not required as not collecting treatment outcome data)
 
○ HADS and HRUQ
 
○ Number of clinician-participant interactions and participant touch points* (Patient approach to the offer and prescription of the first adjuvant treatment)
 
 |

\* Appendix A for definitions

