### **11.2 STATISTICAL ANALYSIS:**

The reporting guideline of CONSORT 2010 statement [7] will be followed for analysis and reporting of this study. All statistical tests and confidence intervals will be two-sided.

Ninety-five percent confidence intervals will be presented with the significance of p value at 5% significance level. Analyses will be conducted on an intention-to-treat basis (all participants who are randomized are included in the statistical analysis, including those who fail to receive an RS result from either the diagnostic core biopsy or excision specimen) and follow a pre-specified statistical analysis plan. Baseline patient characteristics will be tabulated through descriptive statistics. For the primary outcome, comparison of the numbers of participant-clinician touch points will be undertaken using a Negative Binomial model, adjusting for stratification factors and other prognostic baseline covariates. Rate of alteration in treatment pathway and rate of failure of obtaining an RS result on diagnostic core biopsy specimen in the intervention arm will be summarised and a per-protocol analysis will be conducted as secondary analysis, excluding those with alteration in treatment pathway or failure to obtain RS result. Comparison of time between diagnosis and adjuvant treatment will be assessed via Cox regression controlling for the same stratification factors and prognostic covariates. HADS score at baseline, the post-operative result clinic and commencement of adjuvant treatment will be examined by linear regression controlling for the same stratification factors and prognostic covariates. Correlation of preoperative staging with postoperative pathological staging will be calculated.

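### When the post-operative clinic and the adjuvant offer share a date, no rule assigns the single HADS to the after-offer time point, and this is likely to happen more often in the intervention arm

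*Protocol*

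**What the plan says.** Protocol section 3.3 lists as a secondary outcome: "Participant reported anxiety score HADS score at the post-operative result clinic and following the offer of adjuvant treatment". Section 5.1 schedules the forms to match: "The HADS and a health resource utilisation questionnaire will then be completed following the post-operative clinic and following the offer of adjuvant treatment". The next sentence of 5.1 sets the exception: "In the event of the two follow-up events being the same date only the following the post-operative clinic questionnaires will be completed".

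The timing of the RS differs by arm. Section 3.1 says that in the intervention arm "the results of the Oncotype DX® test will be available to be discussed at the post-operative MDT meeting". The table of data collection in section 5.2 has, at the post-operative results clinic, "Oncotype DX® test date ordered (Standard Arm only) RS results delivered (intervention"), and at roughly 2 weeks after that clinic, "RS results delivered (Standard arm only").

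Section 11.2 keeps the later assessment as a separate time point: "HADS score at baseline, the post-operative result clinic and commencement of adjuvant treatment will be examined by linear regression", with adjustment for stratification factors and prognostic covariates, under an intention-to-treat statement covering all randomised participants. Nowhere does the protocol say that a form completed under the same-day exception also counts as the after-offer value.

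**The concern.** Whether a participant has a form labelled after-offer depends on an event after randomisation: the offer falling on the clinic date. The intervention is meant to bring the offer forward (secondary hypothesis, section 2.0), so it is likely to make that event more frequent in its own arm. If the same-day form is filed only under the post-operative time point, the after-offer regression compares nearly all of the standard arm with those intervention participants whose offer came later. Examples are participants whose core-biopsy assay failed or whose offer was made at a further visit.

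Adjustment for baseline covariates does not in general undo selection on a post-randomisation event. At stake is one of the two follow-up anxiety comparisons behind the hypothesis of improved patient experience. The health resource utilisation questionnaire (HRUQ), which feeds the cost analysis in section 10.0, falls under the same exception.

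**Working it through.** **The plan's own figure.** The protocol gives no HADS sample size, so the evaluable numbers for the primary outcome are borrowed. Inputs from section 11.1 and Appendix B: rates 6 (control) and 5 (intervention), allocation 2:1, dispersion 0, two-sided 5%, 90% power. With the null variance taken from the pooled rate:

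- Pooled rate = (6 + 2×5)/3 = 5.333; V0 = 3/(2×5.333) = 0.28125; V1 = 1/6 + 1/(2×5) = 0.26667.
- n control = (1.960×√0.28125 + 1.282×√0.26667)² / (ln 5/6)² = 87.07, rounded up to 88, hence 176 in the intervention arm.
- 88/0.8 = 110 and 176/0.8 = 220.

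The stated 88 + 176 evaluable and 110 + 220 recruited are reproduced, and the present point does not affect them. Using 176 and 88 for HADS assumes the same 20% loss.

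**Is the score lost?** Section 5.2 asks for the post-operative form to be sent within 3 days of the clinic where possible, and the table places its completion at one week ± 4 days. If the offer is made at that clinic, the form is completed after the offer. A valid after-offer measurement therefore exists; only its assignment is missing.

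**Precision if the same-day form is not assigned to the second time point.** Let s be the same-day share in the intervention arm, with 0% in the standard arm. The documents give no value for s, so these are scenarios. In SD units, SE = √(1/[176(1−s)] + 1/88). The full-data value is √(1/176 + 1/88) = 0.1306.

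| s | Intervention n | SE (SD units) | Ratio to full data |
|---|---|---|---|
| 30% | 123.2 | 0.1396 | 1.07 |
| 50% | 88 | 0.1508 | 1.15 |
| 70% | 52.8 | 0.1741 | 1.33 |

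**Selection under the same reading.** Section 1.0 puts the share needing chemotherapy at about 3 in 10. Assume that same-day offers occur only in the other 7 in 10, and that chemotherapy candidates score 2 HADS points higher. Neither assumption comes from the protocol. The chemotherapy share among intervention participants with an after-offer form is 0.3/(1−s), against 0.3 in the standard arm. With no true effect, the arm difference is 2×[0.3/(1−s) − 0.3]:

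| s | Chemotherapy share | Spurious difference |
|---|---|---|
| 30% | 0.429 | 2×0.129 = 0.26 points |
| 50% | 0.600 | 2×0.300 = 0.6 points |
| 70% | 1.000 | 2×0.700 = 1.4 points |

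The last row is the extreme: every non-chemotherapy participant in the intervention arm has a same-day offer.

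**If the standard arm also has same-day offers.** With s = 50% in the intervention arm and 20% in the standard arm, the standard-arm chemotherapy share is 0.3/0.8 = 0.375 and the difference falls to 2×(0.600 − 0.375) = 0.45 points. The SE ratio rises from 1.15 to 1.22. Under these assumptions, equal shares in both arms would remove the selection but not the loss of precision.

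**The case against.** The strongest reply is that the exception only avoids sending a duplicate form. The single form follows the offer, so nothing is lost, and mapping one form to two nominal visits is a derivation rule that an analysis plan, not shown here, could supply. Section 11.2 does not specify a complete-case analysis that drops same-day participants.

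Much of this stands. A reader might infer that the intervention arm has no after-offer HADS in these participants; the timing in section 5.2 contradicts that. A reader might also infer any of the following, none of which the documents establish:

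- **The gap falls mainly in the intervention arm.** RS timing makes this likely, but visits follow local pathways and the first adjuvant treatment may be endocrine therapy or radiotherapy, so same-day offers in the standard arm are not excluded. In either arm, participants whose offer comes at a later clinic complete both forms.
- **The data are missing not at random.** If the value were coded as missing, the gap would be fixed by two event dates, and treatment type and earlier HADS scores are recorded.
- **The bias runs against the intervention.** This depends on an assumed HADS gap between chemotherapy and other patients, which has no source in the protocol.

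What does not stand is that this is merely detail left to the analysis plan. The protocol states a collection rule that labels the form as post-operative only, and it still lists the after-offer score as a separate compared outcome.

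**Conclusion.** The point holds as a gap in assignment, not as lost data. Followed literally, section 5.1 leaves the after-offer HADS empty for same-day participants, and the RS schedule makes it likely that they form a larger share of the intervention arm. The after-offer comparison in sections 3.3 and 11.2 would then rest on subsets selected differently by arm.

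The size cannot be fixed from the documents. Across assumed intervention-arm shares of 30% to 70%, with none in the standard arm, the loss of precision runs from slight to a third. The possible spurious difference runs from about a quarter of a point to 1.4 points, and it rests further on the assumed 2-point gap and on same-day offers being confined to non-chemotherapy patients. The consequence is limited to one time point of a secondary outcome and the matching HRUQ. It is worth correcting because the correction costs almost nothing and should precede analysis in this unblinded trial.

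**What to change.** State in sections 5.1 and 11.2 that, when the two events share a date, the one completed HADS is also the after-offer value. Analyse the after-offer HADS on that basis in all randomised participants with a follow-up HADS, and tabulate the same-day share by arm. Record the second HRUQ period for these participants as zero length, not as missing. In the same edit, align the name of the later time point: section 11.2 ties it to the commencement of treatment, sections 3.3 and 5.1 to the offer.

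The cost is a sentence in each section and a derivation rule, with no extra questionnaires. There are two drawbacks. In same-day participants both time points share one measurement. The post-operative HADS also still follows RS disclosure in the intervention arm and usually precedes it in the standard arm; the rule does not change that, and the report should say so when interpreting that comparison.
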